### Treatment fidelity

The research group comprises licensed and clinical psychologists, researchers, and doctoral student experts in the field of clinical interventions in health care settings and research. Group sessions will be administered by a clinical psychologist with many years of expertise in ACT clinical practice both in individual and group settings, blinded to research scopes. The structure and the content of interventions are consistent with ACT theory. Two bachelor-level observers, also blinded to the research, after a period of training, will attend at least 20% of sessions to evaluate the adherence to intervention protocol, the coverage of contents, and the use of any additional strategies. They will use a checklist detailed for all the content of each intervention, including the process targeted, experiential exercises, and metaphors planned for each session. Coders have to achieve a minimum of 80% reliability with the expert trainers and each other. With lower level of agreement, the data will be dismissed [26].

### Statistical analysis

Data will be analyzed basing on intention-to-treat. This analysis includes all randomized patients in the groups to which they are randomly assigned, regardless of their adherence with the entry criteria, regardless of the treatment they actually received, and regardless of subsequent withdrawal from treatment or deviation from the protocol. Incidence, mechanisms, and patterns of missing data will be explored. To assess if missing data follow a Missing Completely At Random, Little’s MCAR test will be employed. Missing data lower than 5% will be considered negligible. In case of further amount of missing data, multiple imputation will be used.

Sample size has been calculated for a 3 (between) × 4 (within) ANOVA using G*Power software (release 3.1.3) [50]. Setting alpha to 0.05, power to 0.80, and possible dropout, a total sample of 90 is considered enough to detect a small effect size (*f* = 0.20).

Descriptive statistics (such as means, standard deviations, skewness, and kurtosis) will be conducted to explore the characteristics of the sample and assess for the normal distribution of the variables. Differences between baseline characteristics of the sample will be explored using one-way analysis of variance (ANOVA). To assess relations between variables, correlational analysis will be performed. Chi-squared for categorial variables and Pearson’s correlations for continuous variables will be used. To assess the effectiveness of the intervention, mixed between-within 3 (conditions) × 4 (times) repeated measure ANOVAs will be conducted to examine changes from time 0 to time 1, 2, 3, and 4 in means of weight, BMI, and means of scores PGWBI, OQ-45.2, DASS, DERS, DEBQ, AAQ-II, BVI, CAQ, I-CFQ, and FFMQ, between three groups. Corrected effect sizes (Hedges’s *g*) and significance at 95% confidence interval (95% CI) will be calculated for both between-group and within-group differences.

In order to assess adherence to healthy lifestyle recommendations, total means of each daily registered indicator of a healthy lifestyle will be calculated, as well as differences of the same parameters between groups, using one-way ANOVAs.

Analysis will be performed using IBM Statistical Package for the Social Sciences (SPSS) version 26.

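### Below the 5% missing-data threshold, the planned repeated-measures ANOVA would drop randomised patients whom the intention-to-treat statement promises to include

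*Protocol article*

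**What the plan says.** Everything relevant stands in the Statistical analysis section of the protocol article.

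- **Population.** The analysis is by intention to treat: "This analysis includes all randomized patients in the groups to which they are randomly assigned", and this holds "regardless of subsequent withdrawal from treatment or deviation from the protocol".
- **Small amounts missing.** "Missing data lower than 5% will be considered negligible". No handling is named for this case, and the article does not say whether the percentage is of patients, assessments or items, or whether it is taken per scale, per occasion or overall.
- **Larger amounts missing.** "In case of further amount of missing data, multiple imputation will be used".
- **Main analysis.** "mixed between-within 3 (conditions) × 4 (times) repeated measure ANOVAs will be conducted". This label has four times, but the occasions then listed for weight, BMI and the questionnaire scores are five (times 0 to 4).
- **Software.** "Analysis will be performed using IBM Statistical Package for the Social Sciences (SPSS) version 26".
- **Sample size.** "a total sample of 90 is considered enough to detect a small effect size". Dropout is mentioned, but no rate is given.

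**The concern.** A classical between-within ANOVA works on one complete row per patient, and the SPSS procedure for it removes incomplete rows. In the branch where missingness is called negligible, nothing fills the gaps. A patient who misses one follow-up therefore disappears from the analysis of that outcome, including the occasions on which he or she was measured. The same section promises that withdrawal removes nobody. In that branch the promised population and the prescribed method cannot both hold.

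The threshold also looks at the wrong quantity. If it counts missing values, it can stay under 5% while the share of patients lost is several times larger, because deletion works per patient.

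What is at stake is the maintenance question, which the Background names as the most important part of the aim. The Background says that most patients in such programmes do not keep up the healthy lifestyle and regain part of the lost weight. According to Procedures and Discussion, weight and all scales are collected by online survey as self-report. It is plausible, though not documented, that patients who regain weight are the ones who stop answering. Dropping them would make maintenance look better than it is, and could distort the comparison of groups if dropout differs between them.

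**Working it through.** **Inputs from the document.** N = 90 randomised; threshold: missing data below 5%; occasions: five as listed (times 0 to 4), or four as labelled; f = 0.20 and alpha = 0.05.

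**Inputs that are assumptions.** The base of the 5%, the pattern of the gaps, and, for power only, the correlation rho between occasions (sphericity is taken as met).

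**Largest loss under each reading of the 5%**

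| Reading of the 5% | Most that can be missing below 5% | Patients lost from the ANOVA |
|---|---|---|
| Patients | 4/90 = 4.4% (5/90 = 5.6% exceeds it) | 4 of 90 (4.4%) |
| Each occasion separately, times 1 to 4 | 4 patients at each occasion | 4 if the same patients are missing each time; 4 × 4 = 16 of 90 if all differ |
| Pooled assessments, four occasions | 90 × 4 = 360; 17/360 = 4.7% (18/360 is exactly 5%) | at most 17 of 90 (18.9%), leaving 73 |
| Pooled assessments, five occasions | 90 × 5 = 450; 22/450 = 4.9% (23/450 = 5.1%) | at most 22 of 90 (24.4%), leaving 68 |

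The two pooled rows are upper bounds: they need every gap to fall in a different patient. If instead each lost patient misses all four follow-ups, 22 missing assessments correspond to 22/4 = 5.5, so about 5 or 6 patients.

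**A scattered pattern for comparison.** If 4.9% are missing independently at each of times 1 to 4, the expected share of incomplete patients is 1 − (1 − 0.049)^4 = 1 − 0.951^4 = 0.182, or about 16 of 90. This too is an assumed pattern.

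**Effect on power.** For the group-by-time interaction, a noncentral F was used with lambda = f² × N × m / (1 − rho), df1 = (3 − 1)(m − 1) and df2 = (N − 3)(m − 1). With m = 5 and rho = 0.5:

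- N = 90: lambda = 0.04 × 90 × 5 / 0.5 = 36.0, df 8 and 348, power 0.997.
- N = 68: lambda = 0.04 × 68 × 5 / 0.5 = 27.2, df 8 and 260, power 0.976.

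With rho = 0.3 the fall is from 0.969 to 0.896. Only at the extreme of rho = 0 does power go below 0.80, from 0.870 to 0.735. With a loss of 4 patients (N = 86, rho = 0.5) power is 0.995.

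**Above 5%.** Multiple imputation is planned, so all 90 can stay in and no conflict arises.

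**The case against.** The strongest reply is that the problem may rarely occur. If patients drop out in real numbers over nine months, missingness passes 5%, imputation is used and the intention-to-treat set is intact. This stands, and it confines the point to the low-missingness branch. A reader might infer that the whole planned analysis abandons intention to treat; the imputation sentence rules that out.

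Second, deletion of incomplete patients is nowhere written. That is also right. It follows from combining an ANOVA that needs complete rows with a branch in which nothing is imputed. The article offers no other way for such a patient to enter.

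Third, 22 patients is the worst case under one reading. If the threshold is applied occasion by occasion, 22 missing at a single follow-up is 22/90 = 24.4% and triggers imputation. If it counts patients, only 4 can be lost. This stands, so the size has to be given as a range. That one phrase allows both 4 and 22 is itself part of the defect.

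Two further readings are tempting but unsupported. One is that Little's MCAR test decides how gaps are handled. The section lists the test among the explorations of missingness, and the amount missing is the only stated trigger. The other is that the 9-month visit is the designated maintenance endpoint. Follow-ups are set at 3, 6 and 9 months, and none is singled out.

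**Conclusion.** The point holds in limited form. When missingness is below 5%, the plan as written would exclude randomised patients with a missed occasion, contrary to its own intention-to-treat statement. The size runs from 4 of 90 patients to an upper bound of 22 of 90 (17 if only four occasions are analysed), depending on a base that the article does not define and on how the gaps are spread.

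The harm is to the analysis population, with possible bias in the maintenance estimates. The bias cannot be quantified, because the document gives no attrition rate and no reason for dropout. Interaction power is a lesser matter: at an assumed rho of 0.5 it stays above 0.97 even in the worst case.

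The conclusion rests on the ANOVA being run in its usual complete-row form and on no unstated imputation below the threshold. This should be fixed, but it does not undermine the trial.

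**What to change.** Delete the 5% threshold and choose one of two rules for every level of missingness:

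1. apply the multiple imputation already planned, whatever the amount missing; or
2. analyse all observed assessments with a likelihood-based linear mixed model, which SPSS provides.

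Either rule matches the intention-to-treat statement, and the amount missing would no longer select the analysis population. Both assume data missing at random, so neither answers the worry that patients who regain weight stop responding. For that, add a sensitivity analysis that assumes worse (regained) weight after dropout. If a threshold is kept for any purpose, state what it is a percentage of and how gaps below it are handled. The same edit should settle whether four or five occasions are analysed.

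The cost is a few sentences in the analysis section. Data collection, sample size and software stay the same. The change should be made before the outcome data are analysed.

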**Methods:**

A randomized controlled trial will be conducted. Ninety Italian adult inpatients with obesity attending a rehabilitation program for weight loss will be randomly allocated into three experimental conditions targeting respectively each subcomponent of the psychological flexibility model: group Engage focused on values-oriented behaviors, group Openness focused on acceptance and cognitive defusion, and group Awareness focused on being present and aware of thoughts, feelings, and behaviors at every moment. Weight, BMI (kg/m^2^), the Psychological General Well-Being Inventory (PGWBI), the Outcome Questionnaire-45.2 (OQ-45.2), the Depression Anxiety and Stress Scale (DASS-21), the Difficulties in Emotion Regulation Scale (DERS), the Dutch Eating Behaviors Questionnaire (DEBQ), the Brief Values Inventory (BVI), the Committed Action Questionnaire (CAQ), the Italian-Cognitive Fusion Questionnaire (I-CFQ), the Five Facet Mindfulness Questionnaire (FFMQ), and the Acceptance and Action Questionnaire (AAQ-II) will be assessed at the beginning (time 0), at the end of psychological intervention (time 1), and after 3 (time 2) and 6 months (time 3) and 9 months (time 4) from discharge. During the following month after discharge, outpatients will be monitored in their adherence to a healthy lifestyle, using a wearable device.

To assess the effectiveness of the intervention, mixed between-within 3 (conditions) × 4 (times) repeated measure ANOVAs will be conducted to examine changes from time 0 to time 1, 2, 3, and 4 in means of weight, BMI, and means of scores PGWBI, OQ-45.2, DASS, DERS, DEBQ, AAQ-II, BVI, CAQ, I-CFQ, and FFMQ, between three groups.

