## Methods

### Study design

An equivalent randomized controlled trial (RCT) with parallel groups will be conducted. We will perform a simple randomization with 1:1:1 allocation ratio using a computer-generated randomization (www.randomization.com). Allocation concealment will be ensured since all the patients will generate an anonymous code that will be associated to the randomization’s sequence generated by the program. Researchers will be blinded to the association made.

Since we already assessed the efficacy of an ACT-based intervention compared to a CBT-based intervention in the same context of obesity rehabilitation in a previous study [23], in this study, the aim was to compare the three subcomponents of the psychological flexibility model with each other.

Thus, participant enrolled for the study will be randomly allocated into three experimental conditions, targeting respectively each specific subcomponent of the psychological flexibility model:
Group *Engage*Group *Openness*Group *Awareness*

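### Between-arm significance is set at an unadjusted 95% CI with no stated link to the mixed ANOVA; if read for every pair at every follow-up, one outcome carries about a 35% false-positive chance

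*Protocol article*

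**What the plan says.** Under Study design, the protocol article states that "the aim was to compare the three subcomponents of the psychological flexibility model with each other". Allocation is by "simple randomization with 1:1:1 allocation ratio", so there are three arms and three arm pairs.

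Under Statistical analysis, the effectiveness analysis is a mixed 3 × 4 repeated-measures ANOVA for each outcome, looking at change from time 0 to times 1, 2, 3 and 4. The abstract places the later assessments "after 3 (time 2) and 6 months (time 3) and 9 months (time 4) from discharge"; time 1 is the end of the intervention. The next sentence says that bias-corrected effect sizes (Hedges's g) and "significance at 95% confidence interval (95% CI) will be calculated for both between-group and within-group differences".

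The 5% level appears once, in the sample-size statement for the ANOVA: "Setting alpha to 0.05, power to 0.80, and possible dropout, a total sample of 90 is considered enough". The word corrected in the effect-size sentence belongs to Hedges's g, not to the error rate. The section names no deciding pair or time. It gives no adjusted level for arm pairs and does not say whether the intervals are read only after a significant ANOVA.

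**The concern.** A significant three-arm ANOVA shows that the arms differ somewhere. It does not show which component is better. That conclusion must come from Engage vs Openness, Engage vs Awareness and Openness vs Awareness, and the only tool the article gives for these is g with an ordinary 95% interval.

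Three pairs at up to four post-baseline times give up to 12 such intervals for one outcome. Each has a 5% false-positive rate, and together they have far more. Different pairs and times can favour different components. An interval can also exclude zero when the ANOVA is not significant, and the article does not say which result then decides.

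The problem lies within a single outcome. Naming one lead outcome, or correcting across the many questionnaires, would leave it in place.

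**Working it through.** **Inputs from the article:** alpha 0.05 (two-sided assumed, because a 95% CI is used); N = 90, so about 30 per arm; three arms; f = 0.20; power 0.80; a 3 × 4 ANOVA; changes from time 0 to four later times. **Not given, so assumed:** the correlation between repeated measures (varied from 0 to 0.95). No dropout is modelled. A two-sample t interval stands in for the interval around g.

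**1. The article's own figure.** For the group × time test, λ = f² × N × m / (1 − ρ). With m = 4 and ρ = 0, λ = 0.04 × 90 × 4 = 14.4 on 6 and 261 df, and power is 0.814. N = 90 is therefore reproduced, at zero correlation. The sample size and its 5% level belong to this ANOVA, not to the pairwise intervals.

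**2. Number of intervals.** 3 pairs × 4 post-baseline times = 12. The section writes a 3 × 4 ANOVA but lists five times (0 to 4). If the four levels include baseline, there are three post-baseline times and 3 × 3 = 9 intervals.

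**3. Benchmark.** Were the 12 independent, the family-wise rate would be 1 − 0.95¹² = 46%. They are correlated, so the rate has to be simulated.

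**4. Simulation with no arm differences** (20,000 trials per setting, 30 per arm). A pair is called different when |mean₁ − mean₂| / √[(s₁² + s₂²)/30] exceeds the two-sided 5% t value on 58 df.

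| Reading of the rule, one outcome | Chance of any false between-arm difference |
|---|---|
| 12 intervals, change from time 0, equal correlations 0 to 0.95 | 34-35% |
| 12 intervals, change from time 0, correlation decaying with time | 30-32% |
| 9 intervals, change from time 0 | about 27-29% |
| 12 intervals, raw scores | 41% (ρ = 0), 35% (0.5), 29% (0.7), 22% (0.9), 19% (0.95) |
| 3 pairs at one time | about 12% |
| 12 intervals on change, read only after a significant group × time test | about 5% |

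Against the stated 5%, the first row is a 7-fold inflation (35/5) and the single-time row is 2.4-fold (12/5). For change scores with equal correlations, the unstated correlation hardly matters. The wide range comes from raw scores.

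**5. Disagreement between the two tools.** In about 30% of null trials at least one of the 12 change-score intervals excludes zero while the group × time test is not significant.

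**6. When one arm truly differs.** A true effect in the third arm makes the group × time test significant. The two equal arms are then compared at four times at 5% each, and the chance of a false difference between them is about 15%. A prior ANOVA therefore protects the case with no differences anywhere, but not this one.

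**7. The adjusted level.** Bonferroni over 12 gives 0.05/12 = 0.0042 per comparison, that is 99.58% intervals. In the situation of step 6, the error for the equal pair over four times is then at most 4 × 0.0042 = 1.7%.

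**The case against.** The strongest reply is that the article does not state the procedure behind the 35%. The effect-size sentence does not say every pair or every time, and independence from the ANOVA is read from silence. The preceding sentence names the mixed ANOVA as the effectiveness analysis, and alpha and N are tied to it. The interval sentence may be no more than effect-size reporting at the usual 5% level. Post-hoc order and adjustment could sit in a full protocol or analysis plan that is not shown.

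Much of this stands. A reader might infer that the trial will declare differences from 12 intervals regardless of the ANOVA, and so has a 35% error rate as planned. The text does not support that. The 35% is conditional, and with a prior group × time test the rate with no arm differences is about 5%.

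The reply does not remove the point. The article does more than omit a post-hoc method: it states that between-group significance will be taken from a 95% CI. The aim requires pairs. The rate exceeds 5% even at one time (about 12%), and the charitable reading, with the ANOVA first, leaves about 15% for two equal arms when the third differs.

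A further objection concerns the remedy. Moving the decision to a single 2-df test at 9 months would abandon the repeated-measures test that N = 90 was sized for, and the aim covers promotion as well as maintenance. That objection is sound, and the fix keeps the planned ANOVA.

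**Conclusion.** The concern holds in conditional form. The stated rule for between-arm significance is an unadjusted 95% CI with no stated link to the ANOVA, and it does not control error for the comparison of three components.

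Its size depends on the reading. For one outcome with no arm differences it is about 35% over all pairs and four post-baseline times on change from time 0, about 27-29% with three post-baseline times, roughly 19-41% on raw scores depending on the unstated correlation, and about 12% at one time. With a prior group × time test it is about 5% when no arm differs, and about 15% for two equal arms when the third differs. These figures assume 30 per arm, normal data and no dropout.

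The article does not show that the 35% reading is the intended one, so the figure should not be quoted as the trial's error rate. The wording should be settled before any arm is reported as better than another.

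**What to change.** Amend the Statistical analysis section as follows:

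- Keep the planned group × time ANOVA as the deciding test for each outcome on which a claim is to be made.
- Call a pairwise arm difference significant only if that test is significant, and then only at a level adjusted over the pairs and times tested (for example Holm or Bonferroni). If significance is to be read from intervals, Bonferroni over 12 means 99.58% CIs.
- Alternatively, name one time in advance and use Fisher's protected procedure there: the 2-df arm test at 5%, then the three pairs at 5% only if it is significant. With exactly three arms this holds the family-wise rate at 5% at that time (4.8-5.1% in simulation).
- Report every other g and 95% CI as descriptive, without a significance statement.

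The cost is a few sentences and no new data, but fewer pairwise results can be called significant. The single-time option has a further price that should be stated if it is chosen. With N = 90 and f = 0.20, λ = 0.04 × 90 = 3.6 on 2 and 87 df, and power is about 37%, against 81% for the group × time test at zero correlation.

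### Arm-versus-arm inference rests on a Hedges's g whose basis is undefined, with no adjustment for the time 0 value; adjusted contrasts would be at least as precise on any reading, at no cost

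*Protocol article*

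**What the plan says.** All of this is in the protocol article, mostly under Statistical analysis.

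- Effectiveness is assessed by mixed 3 × 4 ANOVAs. These "repeated measure ANOVAs will be conducted to examine changes from time 0 to time 1, 2, 3, and 4 in means of weight, BMI" and in the questionnaire scores, compared between the three groups.
- Next come corrected effect sizes, named as Hedges's g, and "significance at 95% confidence interval (95% CI) will be calculated for both between-group and within-group differences". The quantity on which g is computed is not given.
- On imbalance at entry: "Differences between baseline characteristics of the sample will be explored using one-way analysis of variance (ANOVA"). No step follows from the result, and no covariate is named for any analysis.
- Under Study design, the stated aim is to compare the three subcomponents with each other, and "We will perform a simple randomization with 1:1:1 allocation ratio".
- Under Procedures, weight, height and all the questionnaires are collected at time 0 and at four later times, so each ANOVA outcome has a baseline value.

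**The concern.** The aim is comparative: which component does better than which. A three-group ANOVA can show that the arms differ, but not which pair differs. The only arm-versus-arm inference that the article names is g with its 95% CI, to which it attaches significance.

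In its usual form, a between-group g is a difference in arm means over the pooled between-patient SD, with no baseline term. Eligibility is a BMI of 30 or more with no upper limit, in adults aged 18 to 65, so weight will vary widely between patients. With about 30 per arm, chance differences in starting weight can be several kilograms and would carry through to a follow-up-only comparison.

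The baseline ANOVA does not deal with this. Under randomisation every baseline difference is due to chance, so at the 5% level the test flags about 5% of trials by construction. Nothing is prescribed when it flags, and nothing adjusts for what it misses. At stake is the precision of the pairwise answers.

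**Working it through.** **The plan's own figure.** "Sample size has been calculated for a 3 (between) × 4 (within) ANOVA using G*Power software", with alpha 0.05, power 0.80 and f = 0.20. For the group-by-time interaction, noncentrality = f² × N × m/(1 − ρ), with m = 4, numerator df = 2 × 3 = 6 and denominator df = (N − 3) × 3. With ρ = 0 (or the software's Cohen effect-size option), N = 90 gives power 0.814, so 90 reproduces. That calculation concerns the omnibus interaction and says nothing about the precision of a pairwise contrast.

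**Inputs for the pairwise contrast.** From the article: 90 patients in three arms, so about 30 per arm. Not in the article, hence assumed: weight SD 20 kg (range 15–25); baseline-to-follow-up correlation r = 0.95 for weight (range 0.90–0.97) and r = 0.6 for a questionnaire; equal SDs at both times.

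**Formulas.** The SE of a difference between two arms is SD × √(2/30) × √v, where
- follow-up scores only: v = 1
- change from time 0: v = 2(1 − r)
- adjusted for time 0 (ANCOVA): v = 1 − r²

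**Weight, SD 20 kg, r = 0.95.**
- Follow-up: 20 × √(2/30) = 5.16 kg
- Change: 5.16 × √0.10 = 1.63 kg
- Adjusted: 5.16 × √0.0975 = 1.61 kg

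For an illustrative true difference of 3 kg (the article gives no effect in kg), two-sided 5% power from the noncentral t is 9%, 44% and 45%. Over r = 0.90 to 0.97 at SD 20 kg, adjusted power runs from 26% to 65%, and power on change is within one to two percentage points of it. Over SD 15 to 25 kg, the follow-up SE runs from 3.9 to 6.5 kg.

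**Questionnaire, r = 0.6.**
- Follow-up: v = 1
- Change: v = 2 × 0.4 = 0.80
- Adjusted: v = 1 − 0.36 = 0.64

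Adjustment is worth 1/0.64 = 1.56 times the sample against follow-up scores, and 0.80/0.64 = 1.25 times against change. For a standardised difference of 0.5, power is 48%, 57% and 66%. The gain over change equals 2/(1 + r): 1.33 at r = 0.5 and 1.18 at r = 0.7.

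**Baseline imbalance in weight, SD 20 kg.** The expected absolute gap between two given arms is 5.16 × √(2/π) = 4.1 kg. The expected gap between the heaviest and lightest of the three arms is 1.69 × 20/√30 = 6.2 kg (4.6 to 7.7 kg over SD 15 to 25). By simulation, about 55% of randomisations give a heaviest-to-lightest gap above 5 kg that the baseline ANOVA does not flag.

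**The case against.** A reader might infer that g ignores each patient's baseline, so that the weight comparison mostly shows which arm started heavier. The article does not support this. It never says that g uses raw follow-up means, and the sentence just before it frames the comparison as changes from time 0. If g follows that frame, the loss for weight nearly vanishes (1.63 against 1.61 kg).

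A reader might also infer that the trial as a whole throws power away. The assessment of effectiveness is assigned to the mixed ANOVA, and its group-by-time term uses within-patient change if time 0 is a level of the time factor or is subtracted. That should be clarified, because the layout has four times and the text lists five. The loss shown here belongs to the pairwise estimates.

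Nor can it be said that chance imbalance swamps any component effect. No SD, correlation or effect in kg is given, and the 6.2 kg figure is a three-arm range under an assumed SD, not a pairwise gap. Likewise, nothing says that the within-arm intervals will be unpaired; that is only a point to make explicit.

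Finally, the exact formula for g could sit in a fuller document. That is fair, and an undefined formula alone would not be a finding. But the article itself chooses the statistic, attaches significance to it and chooses significance tests for baseline imbalance. A better method exists for data already collected, whichever formula was meant.

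**Conclusion.** The point holds as a free improvement. Under the usual model with equal SDs at both times, adjustment for the time 0 value is at least as efficient as follow-up scores or change, since 1 − r² never exceeds 1 or 2(1 − r).

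The size depends on the reading and on assumed values. The gain is large for weight and BMI if g is on follow-up scores: the SE is about 3.2 times smaller (5.16/1.61). It is negligible for weight if g is on change. It is moderate for questionnaires even on change, at about 1.25 times the sample for r = 0.6. Questionnaires make up most of the listed primary outcomes, so the moderate gain matters. On any reading, the baseline significance tests leave chance imbalance unaddressed.

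**What to change.** 1. For each pair of arms at times 1 to 4, estimate the difference adjusted for the time 0 value of the same outcome. Report it in original units (kg, kg/m², score points) with its 95% CI, and make this the arm-versus-arm inference.
2. Give Hedges's g only as a rescaling of that adjusted difference by the baseline SD, and state this definition.
3. State that within-arm intervals are computed from paired data.
4. Replace the baseline ANOVAs with a descriptive table by arm.
5. State how time 0 enters the 3 × 4 ANOVA, given five assessment times.

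The cost is analysis wording only. The time 0 values are already scheduled, and no visit, measure or sample size changes.
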